### Intervention

The intervention lasts 3 months and is based on the use of *CuidaconTIC* and the Xiaomi Smart Band 7 activity wristband. Participants will regularly use *CuidaconTIC* services and wear the Xiaomi Smart Band 7 wristband.

*CuidaconTIC* is a technological platform for caregivers developed through the TechQoL4Carers project [34]. The research team designed and developed *CuidaconTIC* through an iterative and participatory process with informal caregivers, the platform’s end users, and other actors involved in care, such as health science professionals.

The platform is integrated into both a website and a mobile application. The services offered include a summary of the individual’s health status, training content, advice, and personalized recommendations based on their QoL, care situation, occupational balance, self-management of health, and empowerment. It also allows for synchronization with the Xiaomi Smart Band 7 activity wristband. *CuidaconTIC*, 1.0 version, will be used for the pilot project. After the trial results are integrated, the final version of the platform will be obtained. The main services of the *CuidaconTIC* platform are: My daily summary, My health, My week, I take care of myself, and I take care of you.

Caregivers are expected to access and use the TechQoL4Carers platform at least once a week to complete the weekly questionnaire and consult the training content related to self-care and care provision at least once a month.

The research team will provide caregivers with the Xiaomi Smart Band 7 wristband to capture health-related data and synchronize it with the platform. Participants are expected to use the wristband daily during the 3-month intervention. These data will be combined with other information collected through subjective measurements to provide personalized content and recommendations.

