Furthermore, given the longitudinal nature of the study, data from wearable devices and scores from the weekly questionnaire will be summarized at the weekly level. For wearable data, daily recordings will be checked for validity and aggregated as weekly averages. Based on previous studies [64,65], a week will be considered valid if it contains at least 4 days with usable recordings. Trends in weekly measurements of sleep, heart rate, and step count, as well as weekly questionnaire scores, will be analyzed using repeated-measures ANOVA or the nonparametric Friedman test, depending on data distribution, including only participants who meet prespecified minimum completeness criteria for the weekly data.

To handle incomplete weekly or wearable data systematically and reduce the risk of biased estimates, the amount and pattern of missing wearable and weekly questionnaire data will be described, and all available valid weeks will be included in the analyses under a missing-at-random assumption. In addition, sensitivity analyses will be performed to assess the robustness of the longitudinal and correlational findings to different assumptions about missing data.

Regarding the qualitative analysis of the final interview, the instructions of the thematic analysis by Braun and Clarke [66] will be followed, who defined 6 phases: (1) familiarizing with the data; (2) generating initial codes; (3) searching for themes; (4) reviewing themes; (5) defining and naming themes; and (6) producing the report. The analysis will be carried out independently by 3 researchers using the previously described inductive approach, and MAXQDA 24 software [67] will be used for the triangulation of the information.

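### The weekly trend analysis promises to use every valid week under missing-at-random, but its participant restriction and named tests cannot do so

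*Protocol article*

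**What the plan says.** The point rests on two consecutive paragraphs of the Analysis section of the protocol article.

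- **Participants.** The weekly trend analysis covers sleep, heart rate, step count and questionnaire score, and it is limited: "including only participants who meet prespecified minimum completeness criteria for the weekly data".
- **Tests.** The same sentence names only two methods for these trends, repeated-measures ANOVA and Friedman, with the choice left to the distribution of the data.
- **Valid week (wearable data).** "a week will be considered valid if it contains at least 4 days with usable recordings". This rule defines a usable week. It does not define when a participant is complete enough.
- **Missing data.** The next paragraph opens with its purpose: "To handle incomplete weekly or wearable data systematically and reduce the risk of biased estimates". It then says the amount and pattern of missing data will be described and that "all available valid weeks will be included in the analyses under a missing-at-random assumption".
- **Sensitivity.** "sensitivity analyses will be performed to assess the robustness of the longitudinal and correlational findings to different assumptions about missing data". No method is named.

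The Intervention section expects caregivers to use the platform "at least once a week to complete the weekly questionnaire" and to wear the wristband daily. The Analysis section classes every outcome other than quality of life as secondary or exploratory.

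**The concern.** The two paragraphs describe different analysis sets. One admits a subset of caregivers and applies tests built for a full participant-by-week table. The other says every valid week counts and relies on missing-at-random (MAR) to justify it. An analyst cannot follow both, and a report could present a complete-case result as an all-available-data MAR analysis.

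Two things are at stake for the steps, sleep and My Week results. The first is precision, because valid data are thrown away. The second is bias. The caregivers who remain are those who kept wearing the band and completing the form, and their trend need not be that of everyone enrolled. The study's main question is about the effect of routine use of the platform, so a set filtered on regular recording needs to be labelled as such.

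**Working it through.** **1. The passages side by side.** Take a caregiver with some valid weeks but fewer than the minimum. The first paragraph excludes this person; the second includes those weeks. Any minimum that excludes someone with valid data produces the conflict, so it does not depend on the threshold's value.

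Now take a caregiver above the minimum with one missing week. Standard repeated-measures ANOVA and Friedman need a complete block, so this person is dropped as well. The article names no mixed model, estimating-equation method or imputation that would use the remaining weeks.

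**2. Inputs.** There are 12 weekly measurements (Table 1 footnotes: weeks 1-6 and 7-12). The denominator is 54 completers (Sample Size). The article gives no figure for the weekly analysis to reproduce. Its power claim for 54 completers concerns the primary paired t test. That claim is correct (two-sided power 0.950 at d = 0.5) and has no bearing here. Weekly validity *p* is not given, so 0.80, 0.90 and 0.95 are assumed.

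**3. Caregivers with all 12 weeks.**

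- Independent weeks: share = p^12.
- Clustered within people: beta-binomial with within-person correlation 0.3 (assumed). Then a + b = (1 − 0.3)/0.3 = 2.333, a = 2.333p, and share = ∏ (a + j)/(2.333 + j) for j = 0 to 11.

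| p | Independent: share | of 54 | Clustered: share | of 54 |
|---|---|---|---|---|
| 0.80 | 0.069 | 3.7 | 0.370 | 20.0 |
| 0.90 | 0.282 | 15.3 | 0.618 | 33.3 |
| 0.95 | 0.540 | 29.2 | 0.788 | 42.6 |

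**4. Threshold or tests?** Suppose the minimum were 9 of 12 weeks (assumed). With independent weeks it would admit about 43, 53 and 54 of 54 at p = 0.80, 0.90 and 0.95. Comparing these with 4, 15 and 29 complete caregivers shows that under a lenient minimum most of the loss comes from the tests.

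**5. Can the trend be biased?** Step 3 shows lost numbers only. Independent missingness of that kind causes no bias, so bias was checked by simulation.

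- *Dropout depends on the previous week's score (MAR).* 62 caregivers, 12 weeks, 200 runs. Person-level intercept SD 1, slope SD 0.06 per week, residual SD 0.6, true mean and true change both zero. Log-odds of stopping were −2.5 − 1.0 × previous score. About 24 of 62 were complete. Complete cases gave a mean level of +0.72 and a change of +0.12. A random-slope mixed model on all available weeks gave −0.03 and −0.05.
- *Wear stops more often after a fall in the caregiver's own steps (MAR).* 54 caregivers, 60 runs, true change −550 steps/day. About 82% of weeks were valid and about 22 caregivers were complete. Complete cases gave about −400. The mixed model gave about −590 (Monte Carlo SE 30).
- *Validity depends only on a caregiver's stable level.* 54 caregivers, 2000 runs, true change −550. Again about 22 were complete. Complete cases gave −540 (Monte Carlo SE 7), so essentially no bias in the change.

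The bias therefore depends on the mechanism. It appears when missingness follows a caregiver's earlier changes, which MAR allows.

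**The case against.** The strongest reply is that this is a wording tension in low-stakes analyses, with safeguards already in the text. Missingness will be described and sensitivity analyses are promised. The all-weeks sentence also covers correlational work, where it can be honoured. Some unbalanced ANOVA routines keep partly observed participants. All of this is fair and lowers the weight of the point. It does not remove the conflict. The sensitivity analyses name no method and do not say which set is the main one. No unbalanced routine is specified, and the participant restriction would remain even with one.

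Several stronger readings are tempting but not supported:

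- *Only near-complete caregivers are admitted.* The text says there is a minimum, not how high it is.
- *The threshold was never fixed, or will be chosen after the fact.* The text calls it prespecified, and the value may sit in a fuller plan. The Abstract says the protocol was submitted before analysis.
- *A missed questionnaire is a week without platform use.* My week is one of five main services, so a caregiver may use the others and skip the form. It is only a week without the expected questionnaire.
- *Complete-case change is unbiased only under missing completely at random.* The third simulation is a counterexample.
- *The tests will reject too often because of serial correlation.* This assumes ANOVA without a sphericity correction, which the text does not specify.

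**Conclusion.** The Analysis section contradicts itself. As written, the weekly trend analysis cannot include all valid weeks and is not valid under MAR in general. It loses data and favours caregivers who kept recording. It can also bias the trend when missingness depends on a caregiver's earlier changes.

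The size cannot be known from the article. Under assumed weekly validity of 80% to 95%, the set with all 12 weeks is about 4 to 29 of 54 with independent weeks, or about 20 to 43 with a within-person correlation of 0.3. Non-wear probably clusters within people, so the independent figures are best read as the pessimistic end. The simulated biases show direction and possibility; they are not predictions for this trial.

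Only secondary or exploratory outcomes are affected. The change should be made, but the trial's confirmatory conclusion does not depend on it.

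**What to change.** Before analysis starts, replace the sentence naming "will be analyzed using repeated-measures ANOVA or the nonparametric Friedman test" with a likelihood-based linear mixed model as the main analysis of each weekly variable. Use a covariance structure that allows for serial correlation, for example a random intercept and slope with first-order autoregressive residuals. Fit it to every valid week of every caregiver with at least one valid week. The missing-at-random sentence then describes what is done.

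Keep the completeness-restricted ANOVA/Friedman analysis as a sensitivity analysis, with its threshold fixed before the data are opened. Report how many caregivers and weeks enter each analysis.

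Dropping the all-weeks sentence and stating the threshold would also remove the contradiction, but it would leave the data loss and selection in place.

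The cost is a change of wording and a few lines of R, with no new data. The Results section says analysis has yet to begin. There are two limits. A parametric model replaces a rank test for skewed variables, so a transformation or bootstrap may be needed. The model is also valid only under MAR, so the promised sensitivity analyses should include departures from it.

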## Results

The project was funded in December 2022, and enrollment was completed in March 2025. As of October 2025, this study has completed the recruitment of participants (N=62). The improvements resulting from the iterative co-design process with caregivers have now been implemented on the platform. Figure 2 shows the main menu of the *CuidaconTIC* platform in Spanish with the main sections: My daily summary, My health, My week, I take care of myself, and I take care of you.

**Figure 2. F2:**
[figure not shown]
Screenshot of the *CuidaconTIC* platform.

The dataset is now being prepared for publication. Data analysis (quantitative and qualitative) will begin next, and the first results are expected to be submitted for publication in June 2026.

## Discussion

### Anticipated Findings

This study aims to develop and evaluate an innovative technological solution aimed at enhancing the QoL, impact of care, occupational balance, self-management of health, and empowerment of informal caregivers of older people and/or people with disabilities.

Technology, empowerment, and the PCC framework can help to improve the caregiver’s health status, QoL, and self-management of their own health. These benefits could extend to the care recipients. Hence, caring for the caregiver has a double effect and greater impact on the social and health systems [68]. The PCC approach is a core element of this research, widely studied in health sciences [21,69,70]. The design and development of the *CuidaconTIC* platform will study the eight PCC dimensions: (1) respect for individuals’ values, preferences, and expressed needs; (2) provision of information and education; (3) access to care; (4) emotional support; (5) involvement of family and friends; (6) continuity and safe transitions; (7) physical comfort, and (8) care coordination.

Person-centered technology has significant potential to support informal caregivers. However, most existing technological solutions primarily focus on care recipients, aiming to promote their autonomy, improve their QoL, and consequently, reduce the burden on caregivers [33,71]. Although there are initiatives targeted at caregivers, they tend to be designed for specific groups, such as caregivers of older adults with dementia, or they primarily provide training and informational services without addressing the broader needs of informal care.

Following a comprehensive analysis of health care and social challenges faced by informal caregivers, this study will propose alternative solutions using person-centered technology. This approach will help advance the field of care and technology as a tool to support caregivers in their daily life.

If the initial hypothesis is confirmed, the study will move toward exploring a low-cost intervention with minimal time requirements, oriented in particular for people with limited availability.

To our knowledge, this is one of the first studies that places informal caregivers at the center of technological development, involving them in an iterative process to create a tool that not only improves care but also directly supports their own QoL, the impact of care, occupational balance, self-management of health, and empowerment.

In summary, this study has the potential to improve caregivers’ perception of their own QoL and health status, promote healthy lifestyle habits, and expand knowledge about care and needs from a preventive perspective.

### Conclusions

This trial focuses on studying the social challenge of the QoL of the caregiver population, mostly women, and on reducing the digital gap and promoting inclusion, through a service that places people and care at the center.

The results of this study will provide an in-depth understanding of the phenomenon of informal care. In addition, it will explore from the perspective of the caregivers themselves what aspects can be interesting to support their daily life through a technological solution focused on the care for caregivers.
